### Complications and shoulder pain medication usage

The investigators who will be blinded to the surgical treatment will be responsible for identifying the complications related to the surgical procedure (e.g., the failure of tendon fixation, pain at the level of the bicipital groove, nerve injury, infection or skin scarring at the surgical site, cosmetic deformity) that might affect each subject throughout the study and follow-up period. Patients will be asked to provide baseline documentation on their medication usage for shoulder pain to be compared with the level of usage reported at the follow-up visits. The generic name, dosage, and frequency of these medications will be recorded. The presence of cramping will be noted following a verbal report from the patient.

### Statistical analysis

The mean, standard deviation and range will be reported for the continuous variables (symptom duration, CMS and SF-36 scores), whereas counts will be used to describe the categorical variables (gender, dominant arm, surgical side, concomitant injuries, disease onset, prior conservative therapies, shoulder tests, surgical technique, cramping, surgical complications, medication usage). Discrete variables will also be analyzed (activity level, LHBT condition). A determination of whether the CMS and SF-36 absolute and percent changes from baseline can reasonably be modeled using Gaussian theory will be performed by examining normal probability plots.

Mean CMS and SF-36 scores will be compared between and within treatment groups at each follow-up using repeated measure analysis of variance (ANOVA) methods on the appropriate scale. The chi-squared test will be used for the comparison of binary measures. If a parametric analysis is feasible, t-tests will be used for the comparison of continuous measures. If the Gaussian model is not appropriate, non-parametric comparison methods will be used on medians, as well as means. In particular, the Mann–Whitney U-test will be used to assess the difference in score distribution between the groups, whereas the Wilcoxon test will be used to compare the scores within the group. The percent of dropouts over time will also be compared in each treatment group. Complications will be compared by treatment group using exact chi-squared methods. Confidence intervals will be reported for the incidence of complications. Age-weighted univariate and multiple stepwise linear and logistic regression analyses will be used to evaluate the relationships between explanatory variables and outcomes with continuous and categorical distributions, respectively. Only explanatory and confounding variables that show a trend toward an association with the outcome of interest (e.g., p < 0.10) in the univariate analysis will be inserted into these models. In the multiple linear regression analysis, total adjusted R^2^ for the model and changes in R^2^ for the independent contribution of single predictors will be calculated to assess the total variance in the outcome variable accounted for by the whole model and single explanatory variables, respectively. In the case of collinearity between the explanatory variables, only the best-fitting models (e.g., those including the collinear explanatory variable accounting for the most relevant variation in the variance of the outcome) will be adopted. A P value of less than 0.05 will be considered significant. The SPSS (SPSS Statistics 17.0, Inc., Chicago, IL, USA) software program for Windows will be used for the database and statistical analysis.

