[15]. To improve studies investigating biceps tenotomy versus tenodesis, the analysis of several variables, including patient demographics, concomitant injuries, CMS, surgical complications, and specific clinical outcomes, such as cramping or cosmetic deformity, has been recommended
[14]. The results of our trial will provide important information to patients and health care providers about the effectiveness of these targeted interventions, possible complications, and predictors of outcome.

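### Change in R-squared from a stepwise model is labelled each predictor's independent contribution; read at the step of entry, it overstates first-entered predictors when predictors correlate

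*Protocol article*

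**What the plan says.** All of this stands in the Statistical analysis section of the protocol article.

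- Model: "Age-weighted univariate and multiple stepwise linear and logistic regression analyses will be used to evaluate the relationships between explanatory variables and outcomes". Candidates for the multiple models first pass a univariate screen, with p < 0.10 given as an example.
- Statistics for the linear models: "total adjusted R^2^ for the model and changes in R^2^ for the independent contribution of single predictors". The stated purpose is to assess the outcome variance "accounted for by the whole model and single explanatory variables, respectively".
- Collinearity: "In the case of collinearity between the explanatory variables, only the best-fitting models" are adopted, explained as "those including the collinear explanatory variable accounting for the most relevant variation in the variance of the outcome". No threshold for collinearity is given.

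The section does not say whether the change in R-squared is taken when a predictor enters or with that predictor entered last. The closing Discussion says that the trial will inform readers about the "effectiveness of these targeted interventions, possible complications, and predictors of outcome", so the predictor results are an advertised product of the trial.

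**The concern.** The plan names a model (stepwise), a statistic (change in R-squared) and an interpretation (independent contribution). On the usual reading these do not fit together. A stepwise procedure adds variables one at a time, and the change at each step credits the entering variable with everything it shares with variables still outside the model. Two correlated predictors of similar importance would then be reported as one strong and one weak, and the strong one's figure would be called independent although part of it is shared.

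Correlated candidates are to be expected here. The plan itself provides for collinearity, and the Baseline and follow-up measurements section collects related items, such as disease onset with symptom duration, and seven shoulder tests.

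A lesser point is scale: the whole model is summarised by adjusted R-squared and the single predictors by what reads as unadjusted changes. At stake is the size of the contributions that readers would take from the predictor analysis.

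**Working it through.** **Inputs.** The plan states no R-squared, regression coefficient or correlation between predictors. All such values below are assumptions, shown over a range. The only planned figure used is n = 128, from the section on the number and source of patients. Its derivation reproduces: with effect size 0.5 and two-sided alpha 0.05, exact t-test power is 0.801 at 64 per group (0.795 at 63).

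**Step 1: two predictors, population values.** Let r1 and r2 be the correlations with the outcome and rho the correlation between the predictors.

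- Total R² = (r1² + r2² − 2·r1·r2·rho) / (1 − rho²)
- Change at entry for the first-entered predictor = r1²
- Unique share of predictor 1 (change when entered last) = R² − r2²
- Unique share of predictor 2 = R² − r1²

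Take r1 = 0.45 and r2 = 0.40. At rho = 0.5, R² = (0.2025 + 0.1600 − 0.1800)/0.75 = 0.243. Predictor 1 enters with 0.203, but its unique share is 0.243 − 0.160 = 0.083.

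| rho | total R² | predictor 1 at entry | predictor 1 unique | ratio | predictor 2 unique |
|---|---|---|---|---|---|
| 0 | 0.363 | 0.203 | 0.203 | 1.0 | 0.160 |
| 0.3 | 0.280 | 0.203 | 0.120 | 1.7 | 0.077 |
| 0.5 | 0.243 | 0.203 | 0.083 | 2.4 | 0.041 |
| 0.7 | 0.217 | 0.203 | 0.057 | 3.6 | 0.014 |

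Order matters: at rho = 0.5, predictor 2 is credited with 0.041 if it enters second and 0.160 if it enters first.

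For two equally important standardised predictors with coefficient b, the entry change is b²(1 + rho)² and the unique share b²(1 − rho²), so the ratio is (1 + rho)/(1 − rho). That is 1.0 at rho = 0, 1.9 at 0.3 and 3.0 at 0.5. With b = 0.3 and rho = 0.5 the figures are 0.2025 against 0.0675.

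**Step 2: simulated stepwise entry.** Settings: n = 128; equally correlated normal predictors; coefficients drawn uniformly from 0.2 to 0.5; residual SD 1; forward entry at p < 0.05; 800 runs per setting, counting those in which at least two predictors entered. Age weighting, the univariate screen and the collinearity rule were not modelled. The table gives the median ratio of the first-entered predictor's change to its unique share in the final model.

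| predictors | rho = 0 | rho = 0.3 | rho = 0.5 |
|---|---|---|---|
| 2 | 1.01 | 1.61 | 2.46 |
| 3 | 1.02 | 2.11 | 3.29 |
| 4 | 1.05 | 2.85 | 5.09 |

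**Step 3: adjusted total against unadjusted changes.** Adjusted R² = 1 − (1 − R²)(n − 1)/(n − k − 1), with n = 128 and k predictors.

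- R² = 0.30: 0.283, 0.271 and 0.253 for k = 3, 5 and 8
- R² = 0.20: 0.181, 0.167 and 0.146 for k = 3, 5 and 8

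Entry-step changes sum to the unadjusted R², so they exceed the adjusted total by about 0.02 to 0.05.

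**The case against.** The strongest defence is that the text does not fix the step at which the change is taken. If each predictor is entered last, the change is exactly its unique share, the word independent is correct, and the main point falls away. A condensed article may leave such a detail to a fuller document. This stands in part: the last-entry reading is possible. It is not stated, though, and in a plan for stepwise models it is not the natural reading. The two readings give materially different figures under one label.

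Three stronger inferences are tempting, and the documents do not support them.

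- *A reader might infer that a promised ranking of predictors will be wrong.* No ranking is promised, only information on predictors. With two predictors the unique shares differ by r1² − r2², so the predictor more strongly correlated with the outcome also has the larger unique share. In the simulation at rho 0.3 and 0.5 the order never changed with two predictors. It changed in about 9% of runs with three and 26% to 31% with four. At rho = 0 it also changed, in 5%, 19% and 37% of runs for two, three and four predictors, through sampling noise. The supportable error is in size.
- *A reader might infer a very large overstatement from the collinearity rule.* With coefficients 0.2 and rho 0.8, the retained variable is credited with 0.04 × 1.8² = 0.130, against 0.04 × (1 − 0.64) = 0.014 in a model with both. The plan would not adopt that two-variable model, and removal from the adopted model also gives 0.130. The rule raises a question of interpretation and does not yield that multiple.
- *A reader might infer that the parts should add up to the total.* The plan never says so, and unique shares do not add up either: in the equal-predictor example they sum to 0.135 against a total of 2 × 0.09 × 1.5 = 0.270. The case for showing both totals is clarity of scale only.

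**Conclusion.** The point holds in a limited form. On its usual reading, the planned change in R-squared is mislabelled as independent, and a first-entered predictor's contribution can be overstated. Under assumed correlations of 0.3 to 0.5 the median overstatement is about 1.6 to 2.5 times with two predictors and more with three or four. It disappears if predictors are uncorrelated or if the change is taken with each predictor last. The size rests wholly on assumed correlations and coefficients.

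The consequence is minor. The statistic belongs to a secondary, exploratory analysis and to the linear models only. The primary comparison of Constant-Murley scores at two years, the complications analysis and the sample size do not depend on it.

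**What to change.** In the Statistical analysis section:

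1. Define each predictor's independent contribution as the fall in R-squared when that predictor is removed from the final model (the squared semipartial correlation), and do not apply the word independent to a step-of-entry change.
2. Report the unadjusted total R-squared beside the adjusted one.
3. Where a collinear variable was dropped, state that the retained variable's contribution may also represent the dropped one.

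The cost is a sentence or two. Part correlations are routine regression output, and no new data or design change is needed. The small downside is that the reported single-predictor contributions will be smaller.

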### Ethics

The trial will be conducted in Fermo (Italy) and Catanzaro (Italy) according to the principles of the Helsinki declaration. Participants will receive information about the study protocol before providing written consent for inclusion in the study. Ethics approval for this study has been received from the Ethics Committee of the “Azienda Ospedaliera Mater Domini”, Catanzaro, Italy, (ref. number 2011–57), which acts as the central ethics committee for this trial. Approval has been obtained from the local ethics committee of the other participating center. With the patient’s permission, an informational letter describing the patient’s participation will be sent to his or her general practitioner. No special insurance will be provided for the patients because the protocol treatments are common surgical procedures routinely used in the centers involved in the study. All participant surgeons will be trained with regard to the study procedures at the beginning of the study.

## Discussion

To the best of our knowledge, this will be the first double-blind randomized controlled trial to compare clinical scores of tenodesis and tenotomy in the treatment of LHBT lesions. There are a few studies in the literature that directly compare the results of these techniques, and most of them reveal no differences between treatments
[11,24-26,49,50]. Boileau *et al.* retrospectively evaluated 68 patients with irreparable rotator cuff tears treated with isolated arthroscopic biceps tenotomy or tenodesis and reported similar outcomes after both procedures
[24]. Osbahr *et al.* retrospectively studied 160 patients with chronic refractive bicipital pain, treating half of the patients with tenotomy and the other half with tenodesis
[49]. They found no significant difference between the two treatment methods in terms of cosmetic deformity, muscle spasm or anterior shoulder pain. Similarly, when twenty patients who underwent biceps tenotomy or tenodesis for chronic tenosynovitis were compared retrospectively, no difference in the functional or cosmetic results was observed
[50].

Wittstein *et al.* showed no significant difference in postoperative scores between the two techniques in a cohort study of 35 patients
[25]. The major limitations of this study were a lack of randomization of participants receiving tenotomy or tenodesis and a limited number of participants. In agreement with a retrospective study
[11], the authors also found that tenotomy decreased forearm supination compared with tenodesis. These findings were not confirmed in other studies, which reported no difference between these techniques
[16,24,26]. Shank *et al.* compared the forearm supination and elbow flexion strength of the upper extremity and found no significant difference between the tenotomy, tenodesis, and control groups
[26]. However, they did not report the clinical scores after these surgeries
[26]. Koh and colleagues demonstrated that neither clinical scores nor total surgical times revealed significant differences between tenotomy and tenodesis
[16]. Notably, this study was not a randomized trial, and the study group was underpowered for most of the outcomes. Therefore, the authors acknowledge that their results should be interpreted with care.

The need for appropriately powered, well-conducted, randomized, controlled trials that compare the outcomes of these procedures has recently been emphasized
[15]. To improve studies investigating biceps tenotomy versus tenodesis, the analysis of several variables, including patient demographics, concomitant injuries, CMS, surgical complications, and specific clinical outcomes, such as cramping or cosmetic deformity, has been recommended
[14]. The results of our trial will provide important information to patients and health care providers about the effectiveness of these targeted interventions, possible complications, and predictors of outcome.

## Abbreviations

BP: bodily pain; CMS: Constant-Murley score; GH: general health perceptions; LHB: long head of the biceps; LHBT: long head of the biceps brachii tendon; MCS: Mental Component Scale; MH: general mental health; MRI: magnetic resonance imaging; NSAIDs: non-steroidal anti-inflammatory drugs; PCS: Physical Component Scale; PF: physical functioning; RE: role limitations due to emotional problems; RP: role limitations due to physical health; SF: social functioning; SF-36: short form 36; SLAP: superior labrum tear from anterior to posterior; VT: vitality energy, or fatigue.
